### Eligibility and informed consent

Coordinators, principal investigators and the chief investigator, all appropriately trained, will obtain consent. Individuals will be recruited from haematology/sickle/respiratory clinics and will be eligible if they give informed consent or assent for children, are aged > 8 years with HbSS diagnosed by standard techniques (HPLC, IEF and MS) and have overnight oximetry showing mean overnight saturation of < 90% for < 30% of the night (i.e. they do not meet current recommended levels of overnight oxygen desaturation for referral for overnight oxygen therapy). Individuals will be excluded if they already have overnight respiratory support, if they have existing respiratory or decompensated cardiac failure or if they have any contraindications to APAP therapy. If participants present with sinus or middle ear infections, they are to be excluded until the infection has been treated and resolved. They may then be evaluated for trial eligibility.

### Randomisation

Central randomisation by computer by the company ‘Sealed Envelope’ will be used with a minimisation algorithm [44] incorporating a random element, stratifying by baseline oximetry minimum overnight saturation (<90% vs ≥ 90%), whether or not a participant is currently prescribed hydroxyurea, presence or absence of infarction on MRI and age group: 8–11 vs 12–15 years in children, and 16–22 vs ≥ 23 years in adults. To ensure maximum balance is achieved across the stratification factors, minimisation will be carried out on these factors separately. Individuals will be randomised to APAP + standard care or standard care alone. The coordinator will be informed of the allocation by email and will arrange for the respiratory physiologist to set up APAP at home for those randomised to APAP.

### Sample size

This study consists of two separate and independent cohorts. The first cohort will consist of 30 children (aged 8–16 years) randomised 1:1 to either APAP or standard of care. The second cohort will consist of 30 adults (aged ≥ 16 years) randomised 1:1 to APAP + standard care or standard care alone. Each cohort represents an independent trial with 90% power to detect a difference in cancellation rate at a significance level of 0.05. Since the cohorts are independent and each has a type I error allocation of 5%, no adjustments for multiple comparisons are needed. Any analyses pooling the child and adult cohorts will be considered exploratory.

In the previous pilot study in children, the results of the cancellation task within each subject group were normally distributed with standard deviation 2, resulting in a mean score difference between APAP treatment and standard care at six weeks of 2.6. Based on this finding, 24 evaluable participants (in each cohort) will provide 90% power to detect a difference in the primary outcome of 2.6 while preserving a significance level of 0.05 (two-sided). This calculation assumes that there is a moderate correlation of 0.5 between the baseline and follow-up measures, and accounts for model adjustment for baseline score [45]. Allowing for 20% withdrawal/loss-to-follow-up, a sample size of 30 individuals randomised 1:1 into two groups will have > 90% power to detect a difference of 2.6 points in cancellation using an analysis of covariance (ANCOVA) model to adjust for the baseline cancellation measure and minimisation factors. The same design characteristics will be used for the adult cohort and the child cohort. Though the values used in the sample size calculation were derived from a cohort of children, no pilot data for adults are available, and the mechanisms by which the treatment effect may be different for adults and children are currently unknown.

### Outcomes

The primary outcome is change from baseline to six months post randomisation in cancellation, a measure of visual attention and processing speed. Secondary outcomes are changes in cognition, pain intensity, quality of life, daytime oximetry, brain MRI and cardiac investigations. Health economic measures will determine quality of life measures in quality-adjusted life years (QALY) terms and the main cost drivers in terms of therapy resources, equipment and travel, etc., and any change in use of other resources, e.g. requirement for transfusion, opioids, other pain relief and hospital admissions to provide a preliminary estimate of the cost of overnight respiratory support compared to standard care. AEs and evidence of bone marrow suppression are key safety outcomes.

### Data collection

Data collection is summarised in Fig. 1. Baseline assessments include demographics, medical history, concomitant medications, physical examination, sleep habits, [46] Epworth Sleepiness instrument [47] and measurements of pain burden [48] and daily pain as well as quality of life using the CHU-9D21 in children [49] and the Euroqol EQ-5D22 in adults [50] as well as the sickle module of the PEDS-QL [51]. Physiologic tests at baseline include a brain MRI and overnight oximetry, which are required for minimisation, as well as daytime oximetry and laboratory measures. The baseline cognitive outcomes assessment is also required before randomisation. Whenever possible, investigators are encouraged to perform heart MRI, echocardiography and a 6MWT.

**Fig. 1 Fig1:**
[figure not shown]
Data collection

Study flow from randomisation through follow-up is shown in Fig. 2. Two weeks after commencement of randomised treatment, individuals will have a face-to-face review for AEs and adherence, and will have daytime oximetry and blood and urine tests. Participants will also have a repeat overnight oximetry at home. Face-to-face assessments for AEs, adherence, daytime oximetry, blood and urine will also take place at months 3 and 6. At months 1, 2, 4 and 5, individuals will be contacted by the study coordinator for review of AEs, treatment adherence and administration of the sickle cell pain burden questionnaire [48].

**Fig. 2 Fig2:**
[figure not shown]
Study flow

At the end of the trial (month 6), participants will undergo end of study tests, including blood and urine tests, medical review, review of adherence and AEs, quality of life, executive function testing and MRI of the brain unless contraindicated. Whenever possible, echocardiography, a 6MWT and heart MRI will also be performed.

Data will be collected on paper case report forms to be stored in a locked cabinet and later double-entered into data management software password-protected and stored securely.

### Cognitive outcomes

Several studies have shown an association of nocturnal hypoxia and sleep-disordered breathing with cognitive impairment, including deficits in processing speed, visual attention, executive function and memory. Moreover, improvement in processing speed has been demonstrated in the general population with OSA following adenotonsillectomy [52] as well as in patients with SCA treated with APAP [18]. In light of these findings, a battery of cognitive tests will be used to track cognitive outcomes in the current study.

In the two weeks between recruitment and randomisation, and again at the end of the study, a psychologist blind to treatment arm will administer standardised tests applicable and comparable in children and adults, with demonstrated validity and reliability, to examine cognitive domains which may improve if overnight desaturation is relieved and sleep improves.

The baseline cognitive assessment will measure general cognitive ability using the Wechsler Abbreviated Scale of Intelligence (WASI), and processing speed, working memory and cancellation using the Wechsler Intelligence Scale for Children-IV ([WISC-IV], age < 16 years) or Wechsler Adult Intelligence Scale-IV ([WAIS-IV], age > 16 years). The Wechsler scales were chosen as they have normative scores validated in a representative sample, including ethnic minorities, in the UK, show strong reliability and validity, are widely used in the literature and are frequently used measure of cognitive function in sleep apnoea as well as SCA, with demonstrated sensitivity to dysfunction in SCA as well as to change following APAP [18]. Moreover, the Wechsler scales have an extensive empirical database, rigorous standardisation procedures and robust psychometric properties, including well-replicated validity, stability and reliability. The cancellation subtest can be administered across a wide age range with age-adjusted scaled scores that are in the range of 1–19. A scaled score of 8–12 is considered to be within the average range.

In addition, on the basis of previous research suggesting sensitivity to dysfunction in SCA, executive function will be assessed using the Tower and Sorting subtests of the Delis–Kaplan tests of Executive Function [D-KEFS], and via parent- (<16 years) or self- (>16 years) report using the BRIEF questionnaire. The BRIEF-questionnaire is sensitive to atypical variations in executive function (EF) development [53] and is the most commonly used screener questionnaire for executive dysfunction. It is either used as self- report for adults (i.e. 18 and 90 years) or given to the child’s parents (i.e. caregiver) to answer questions about either their own or their child’s executive functioning or self-regulation on their everyday behaviour. It is considered an ecologically valid alternative to lab-based assessments [54] and consists of 86 (parent) or 75 (self) questions related to everyday behaviours associated with executive function. It comprises eight subscales (Inhibit, Shift, Working memory, Plan/Organise, and Emotional Control, Initiate, Monitor, Organisation of Materials and Inhibitory Self-Control) that create an overall summary score (General Executive Composite). Higher scores indicate poorer EF. Visual and verbal memory will be assessed using ‘Dot locations’ and ‘Word pairs’ subtests of the Children’s Memory Scale ([CMS] < 16 years) and ‘Designs’ and ‘Verbal Paired Associates’ subtests of the Wechsler memory scale ([WMS] > 16 years). Attention will be measured using Conner’s Continuous Performance Test-III (CPT-III).

### Brain MRI

All participants will undergo MRI at baseline and, unless contraindicated, at study exit. MRI will be performed on a 3-T Siemens Prisma (Erlangen, Germany) at Great Ormond Street Hospital without sedation or contrast agents. MRI protocol of clinical sequences will consist of:T2‐weighted sequenceFluid‐attenuated inversion recovery (FLAIR) sequenceMagnetic resonance angiography (MRA) sequence of the vessels of the Circle of Willis in the brain

These images will be read at baseline and exit by a neuroradiologist blinded to treatment arm who will diagnose SCI and any other clinically significant finding.

The MRI protocol for quantitative analysis blind to treatment arm includes:3D T1‐weighted sequence for volumetric analysis and segmentationDiffusion tensor imaging (DTI) sequence for voxel‐wise white matter analysis and whole-brain tractographyArterial spin labelling (ASL) sequence for non‐invasive measurement of perfusion

MRI results will be assessed blind to treatment arm in two ways. Any change in radiological status (i.e. change from normal study, new or enlarged SCI, any other clinically significant change from baseline) will be recorded. For quantitative imaging analyses: (1) a longitudinal TBSS design will be implemented to show change in white matter metrics between treatment groups and correlations with change in haematological or cognitive outcomes; (2) global and regional cerebral blood flow maps will be calculated to show differences between treatment groups and correlations with change in haematological or cognitive outcomes; (3) volumetric segmentations of surface area, cortical thickness and grey matter volume will be calculated at each time point and differences will be compared between treatment groups as well as correlations with change in haematological or cognitive outcomes.

### Compliance

For the APAP arm, adherence to treatment will be formally assessed using specially designed software (Encore Pro™ data management software) and Smartcard which records and saves both qualitative and quantitative data on a single downloadable card. Compliance will be assessed regularly. Adequate adherence will be defined as use of the APAP for at least 4 h a night and at least 16 nights per month. A subgroup analysis of subjects using APAP for at least 4 h on the night before cognitive assessments will be evaluated

### Pain

Monitoring of daily pain will occur daily for two weeks at two separate time-points: baseline and end of study. Assessments will be performed using a Smartphone e-Diary (GoMed Solutions Inc), taking < 5 min per day to complete, which downloads anonymous data to a web-based database. This application collects information including whether or not pain was experienced and if it was, further questions on pain characteristics as follows: (1) current pain, using a 0–10 electronic numerical rating scale (e-NRS); (2) the highest e-NRS in past 24 h; (3) the lowest e-NRS in past 24 h; (4) the average-e-NRS in the past 24 h; (5) location of pain on a body outline diagram; (6) how much pain interfered with everyday activities in past 24 h; and (7) descriptors of pain to characterise its nature as neuropathic or nociceptive. The same information may also be collected on a paper form. In addition, pain characteristics and descriptors will be collected at the end of every month via a phone call using the Pain burden questionnaire [48]. Pain-related healthcare visits over the entire period, including admissions for pain (reported as expected serious adverse events), will be compared between the two arms to assess whether the intervention has an impact on hospital attendance and admission.

### Quality of life

Quality of life will be measured using the PedsQL, which contains a validated sickle module for use in adults and children [51]. Additionally, the utility measures CHU-9D and Euroqol EQ-5D [50] can be used for children and adults, respectively. These are preference-based quality of life measures that will be employed in estimating QALYs. As this is a study of an intervention for sleep, it is also important to use sleep questionnaires, specifically the Sleep Habits screener [46] and Epworth Sleepiness scale, [47] to document features such as snoring. This study provides the opportunity to assess the feasibility, acceptability and comparative performance of these measures in assessing SCA-related symptoms and quality of life.

### Statistical analysis

Analyses will be performed in accordance with the intention-to-treat principle, though a ‘per-protocol’ subgroup with adequate treatment adherence will be defined before database lock. The primary analysis of change in cancellation time will be based on an ANCOVA model containing the baseline cancellation score and minimisation factors as fixed covariates. A sensitivity analysis excluding the minimisation factors will also be performed. Pre-specified subgroups include the minimisation factors and the subgroup of individuals with adequate APAP compliance on the night before cognitive testing. Continuous variables that are collected at baseline and six months will be analysed using similar models. Pain and other outcomes with multiple collection points will be analysed using mixed models for repeated measures, based on observed data and including the fixed, categorical effects of treatment, minimisation factors, visit and treatment-by-visit interaction, as well as the continuous, fixed covariates of baseline and baseline-by-visit interaction. An unstructured covariance will be used to model the within-patient errors if possible; compound symmetry will be used otherwise. Binary outcomes will be analysed using logistic regression, including the minimisation variables as fixed covariates.

The overall significance level of 5% will be allocated for the primary analysis. Type 1 error adjustments for secondary outcomes will not be made and analyses beyond the primary outcome should be interpreted with caution.

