## Methods and design

This is a single-blind randomised controlled phase II trial consisting of two separate cohorts of people with HbSS (children and adults) recruited through two London National Health Service hospitals in the UK (Guy’s and St Thomas’ NHS Trust and King’s College Hospital NHS Trust, both academic centres as part of King’s Health Partners). Though some pooled analyses may be conducted, the cohorts are independent and will be analysed separately. Informed consent/assent will be obtained from all participants in the study. After randomisation, individuals assigned to APAP will be provided with a REMstar® Auto System, which is an APAP device designed for the treatment of OSA and is supplied by Respironics. When set in the Auto‐APAP mode, the system will monitor breathing during sleep and automatically adjust the pressure to meet therapeutic needs. Individuals in the APAP arm will use this intervention nightly for six months. Individuals randomised to standard care will have treatment according to routine National Health Service procedure for sickle cell disease for six months post randomisation.

The intervention involves wearing a mask for several hours most nights, so it is difficult to justify a sham treatment arm of six months of overnight respiratory support. The outcomes will be assessed by study personnel blind to treatment arm so that although the family and some professionals involved in data collection know the treatment allocation, the assessors of endpoints, including cognitive function, imaging, pain frequency and quality of life, will not know the treatment assignment. All study personnel not directly involved in treatment administration and compliance will be blinded to randomisation assignment until the blind is broken for each cohort. Blinded study personnel include data managers and the trial statistician, as well as assessors of endpoints.

APAP dose reductions are permitted if required, e.g. in the case of AEs. Discontinuation of participants from the trial will occur if there is withdrawal of a child’s assent to participate or participant/parental/guardian withdrawal of consent to participate or loss to follow-up; wherever possible the primary and secondary endpoint will be collected.

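### The night-before and per-protocol subgroups rest on APAP use after randomisation, so they cannot serve as treatment-effect subgroups, and any comparison of them with controls is non-randomised

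*Protocol article*

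**What the plan says.** All references are to the protocol article.

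- **Compliance** sets the measurement: "For the APAP arm, adherence to treatment will be formally assessed using specially designed software". The rule is "Adequate adherence will be defined as use of the APAP for at least 4 h a night and at least 16 nights per month". The section then adds: "A subgroup analysis of subjects using APAP for at least 4 h on the night before cognitive assessments will be evaluated".
- **Statistical analysis** makes intention-to-treat the main principle, "though a ‘per-protocol’ subgroup with adequate treatment adherence will be defined before database lock". Its list of pre-specified subgroups holds the minimisation factors and "the subgroup of individuals with adequate APAP compliance on the night before cognitive testing". It allocates the 5% level to the primary analysis and advises caution about everything else, because there is no type 1 error adjustment for secondary outcomes.
- **Methods and design** gives controls standard care with no sham device. On blinding it says: "Blinded study personnel include data managers and the trial statistician, as well as assessors of endpoints". Staff directly involved in treatment administration and compliance are outside the blind.

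**The concern.** A treatment-effect subgroup needs a factor that is defined in both arms and that treatment cannot influence. The minimisation factors (age group, infarction on MRI, minimum overnight saturation, hydroxyurea) qualify. Use of APAP on one night about six months after randomisation does not. It arises after allocation, and it does not exist for someone without a device. The per-protocol subgroup has the same structure.

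If the qualifying APAP users are set against the controls, one arm has been filtered and the other has not. Participants who managed at least 4 h on the mask before the test may differ in sleep, pain or motivation from those who did not, and controls with equally bad nights stay in. The endpoint is a test of visual attention and processing speed, on which such differences could plausibly bear. A spurious difference could then appear in an analysis that carries the standing of pre-specification. Pre-specification prevents choosing subgroups after seeing results; it does not restore randomisation.

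A smaller issue concerns blinding. If fixing the per-protocol set before lock means classifying individual patients, the data needed exist only for APAP patients and would reveal allocation to anyone who sees them.

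**Working it through.** **1. The plan's own figure.** The Sample size section gives SD 2, correlation 0.5, difference 2.6, two-sided 0.05, 24 evaluable and 30 randomised per cohort.

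- Residual SD after baseline adjustment: 2 × √(1 − 0.5²) = 1.732.
- Power with 12 per arm, t-based ANCOVA: 93.9%, so the stated 90% is met.
- Loss to follow-up: 24 / (1 − 0.20) = 30.

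The sample size reproduces and is not in question. It supplies the residual SD used below.

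**2. Can the subgroups be formed in both arms?** Adherence is recorded for the APAP arm only, controls have no device, and both definitions are in hours or nights of APAP use. Membership is therefore undefined for every control.

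**3. Size of the bias if qualifying APAP users are compared with all controls.** Let *p* be the share of the APAP arm that qualifies and *r* the correlation between adherence propensity and the outcome residual. The documents give neither, so both are assumptions. Suppose there is no treatment effect and the qualifiers are the top *p* of a normal propensity. The expected spurious difference is then

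bias = r × 1.732 × φ(z) / p,

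where z is the cut-off that leaves a share *p* above it and φ is the standard normal density.

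- p = 0.5: φ/p = 0.399/0.5 = 0.798, so bias = 1.382 r
- p = 0.7: φ/p = 0.348/0.7 = 0.497, so bias = 0.860 r
- p = 0.9: φ/p = 0.175/0.9 = 0.195, so bias = 0.338 r

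The table also gives the two-sided type I error from simulation (12 per arm, ANCOVA on baseline, 8,000 replicates per setting).

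| r | Bias, p = 0.5 | Type I error, p = 0.5 | Bias, p = 0.7 | Type I error, p = 0.7 | Bias, p = 0.9 |
|---|---|---|---|---|---|
| −0.3 | −0.42 | 7.3% | −0.26 | 6.0% | −0.10 |
| 0 | 0 | 5.0% | 0 | 4.8% | 0 |
| 0.3 | +0.42 | 7.2% | +0.26 | 5.9% | +0.10 |
| 0.5 | +0.69 | 10.6% | +0.43 | 8.1% | +0.17 |
| 0.6 | +0.83 | about 14%* | +0.52 | not run | +0.20 |

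*From a separate simulation with the same residual SD and arm size.

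The sign of the bias is the sign of *r*. It vanishes at r = 0 and when everyone qualifies. The largest entry is 0.83/2.6 = 32% of the design difference.

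**4. What a randomisation-based alternative costs in precision.** The complier-average causal effect is the intention-to-treat difference divided by *p*, because no control can be adherent. With 12 per arm:

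- Standard error of the intention-to-treat difference: 1.732 × √(2/12) = 0.707.
- 95% half-width: 2.08 × 0.707 = 1.47.
- Dividing by *p* (treated as fixed): 1.47/0.5 = 2.94, or 1.47/0.7 = 2.10 points.

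The method assumes that allocation has no effect in those below the threshold. If they gain δ points, the estimate is too high by δ(1 − p)/p. That is 1.0 × δ at p = 0.5 and 0.43 × δ at p = 0.7.

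**The case against.** - **The comparator is not stated.** The article says only that the night-before group will be analysed. A description within the APAP arm is not excluded, and the detail may be in the analysis plan that is not shown. This stands, and the point is therefore conditional. The text still leans towards a between-arm reading: the group sits in the list for the treatment comparison, and the Discussion says practice effects may raise scores in both arms and make a control group necessary. If a within-arm description is meant, it does not belong in that list.
- **The direction is not established.** A reader might infer that the subgroups are biased towards APAP. The documents give no relation between adherence and score. The Background says the main problem is non-compliance when the nuisance does not seem worth the benefit, so persistent users could be the more symptomatic. This stands: a gain for APAP is plausible, not shown.
- **The size rests on assumptions.** The only compliance figure in the article is that all 12 children in a six-week trial were compliant. High adherence makes the bias small, as the p = 0.9 column shows, and r = 0.6 after baseline adjustment is extreme. This stands.
- **The blind is not necessarily broken.** A reader might infer that the statistician is bound to be unblinded. The text can mean that only the criterion is fixed before lock, the criterion is already in the Compliance section, and compliance staff are outside the blind. A risk remains only if patients are classified by, or in view of, the blinded statistician.
- **The primary analysis is safe, and caution is already advised.** The first part is right and limits the severity. The caution concerns multiplicity and does not disclose selection bias.

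**Conclusion.** The point holds as a defect of moderate severity in supportive analyses. It is certain from the text that both subgroups depend on APAP use after randomisation, measured in one arm, and so cannot be treatment-effect subgroups. If they are compared with controls, the result is non-randomised, with a bias of unknown size and sign. The range of about −0.4 to +0.8 points rests on assumed values: 50–70% qualifying, correlation −0.3 to 0.6, residual SD 1.73 from the plan's own inputs, and the full control arm as comparator. The documents do not support a claim that the trial's main result is compromised: the intention-to-treat ANCOVA, its error rate and the sample size are untouched.

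**What to change.** 1. Take the night-before group out of the pre-specified treatment subgroups. Report it descriptively within the APAP arm, labelled non-randomised.
2. Label any per-protocol comparison with controls exploratory and non-randomised, and state which controls it uses.
3. Add, or substitute, a supportive complier-average causal effect analysis. Use randomisation as the instrument, the adherence rule already in the Compliance section, the same baseline covariates as the primary model, and all randomised participants. State its exclusion assumption, and that benefit in partial users would inflate the estimate.
4. State that unblinded compliance staff apply the adherence rule, or that it is applied after lock, so that patient-level adherence data do not reach the blinded statistician beforehand.

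The cost is a few sentences and one changed supportive analysis, with no new data. The main drawback is precision: with 24–30 participants per cohort the complier estimate will have a wide interval. If labelling alone is preferred, items 1, 2 and 4 remove the misleading status, but they leave no randomisation-based estimate of the effect in adherent participants.
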